#### Secondary outcomes

One of the secondary outcomes is the exacerbation frequency as indicated by medication use. This is one of the classical COPD outcomes, and exacerbations have a large impact on patients’ lives.

Other secondary outcome parameters are changes in CCQ score, 6 minute walking distance test, HADS, mMRC, lung function, and differences between the two groups in hospital admissions and mortality.

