#### Sample size calculation

Sample size calculations are based on difference in change in health status between both groups. Because the intervention is guided by the CCQ, an alternative health status scale, the SGRQ, is used for the power-calculation. Based on 80% power to detect the minimal clinically important difference (4 points on the SGRQ) between the two groups, a sample size of 150 persons per group is needed. The standard deviation of the SGRQ total score in different samples is approximately10-17 (12 used in calculation) [38-42]. The alpha level was set at 0.05.

Taking dropouts into consideration, a sample size of 165 patients / group = 330 patients in total is aimed for.

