### Statistical analysis

The primary outcome measures is the change in SGRQ over time. The SGRQ results in a total score and 3 subscale scores: symptoms, activities and impact. The SGRQ change in scores over the treatment period of the control group will be compared to that of the experimental group. The scores will be tested for normality. In case of normality the difference will be univariately tested with a student T-test and multivariately with a linear regression model. In case of deviation from normality the variable will be transformed to normality via a Box-Cox transformation and thereafter analyzed via student T-test and linear regression models.The multivariate models will be corrected for the following confounders: educational level, age, gender, current smoking, and FEV_1_. The number of exacerbations will be reported as weighted exacerbations rates (total number of exacerbations divided by the total person-time of follow up per group) [43-45]. Statistical significance of weighted rate ratios will calculated using a Poisson regression model. The secondary research outcomes will be tested in a similar fashion as the primary research question. The primary analyses will be based on the intention-to-treat principle. As secondary analyses, a per protocol analysis will be performed to increase insight in the data.

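### The Poisson test of the exacerbation rate ratio makes no allowance for overdispersion, so its p-value and confidence interval are likely to be too optimistic

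*Protocol article*

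**What the plan says.** The Secondary outcomes section states: "One of the secondary outcomes is the exacerbation frequency as indicated by medication use". It is the first secondary outcome named, and exacerbation frequency also appears in the second research question.

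The Statistical analysis section defines each group's rate as "total number of exacerbations divided by the total person-time of follow up per group" and continues: "Statistical significance of weighted rate ratios will calculated using a Poisson regression model". Nothing is said about overdispersion, a robust or scaled variance, or another count model. The same section lists the adjustment variables for the multivariate models (educational level, age, gender, current smoking and FEV1) and says that secondary outcomes are handled much as the primary outcome is. It does not say whether the adjustment extends to the exacerbation model.

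The significance level appears once, under Sample size calculation: "The alpha level was set at 0.05".

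**The concern.** A Poisson model sets the variance of a patient's count equal to its mean. That holds if all patients with the same covariate values have the same underlying rate. If some of them are more prone to exacerbate than others, the counts vary more than the model allows. The standard error of the log rate ratio is then too small, the interval too narrow and the p-value too low.

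The article gives two reasons to expect this:

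- The Discussion says that functional status, as measured by health status questionnaires, has been shown to predict exacerbations. Rates therefore differ by a patient characteristic that is not a listed covariate.
- Selection and recruitment sets no limit on FEV1 or on exacerbation history. Exacerbations in the last year are recorded at baseline (Measurements) but are not a listed covariate either.

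At stake is a claim of benefit or harm on exacerbations that rests on an understated standard error. The article names fewer exacerbations as one of the two aims of primary-care COPD treatment, so such a claim would weigh in any decision to adopt the algorithm.

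**Working it through.** **The plan's own figures.** The article gives no rate, dispersion or power for exacerbations, so there is nothing to reproduce for this outcome. Its only calculation is for SGRQ (4 points, SD 12, 80% power, two-sided 5% assumed):

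n = 2 × (1.960 + 0.842)² × 12² / 4² = 141.3, so 142 per group.

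The article states "a sample size of 150 persons per group is needed", which gives 82.3% power and is slightly conservative. It has no bearing on this point. The planned 165 per group (150 × 1.10) and the 2-year follow-up are used below.

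**Formula.** Let r be the annual rate and k the between-patient variance of the rate relative to its mean squared. The mean count is μ = 2r. With gamma-distributed patient rates the variance of a count is μ + kμ², so the variance exceeds the Poisson value by the factor

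φ = 1 + kμ.

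The true standard error is √φ times the Poisson one. The nominal two-sided 5% test has actual size

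α = 2 × [1 − Φ(1.96/√φ)],

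and the interval on the log scale is too narrow by 1 − 1/√φ.

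**One case in full.** With r = 0.5 and k = 0.5, μ = 1.0, φ = 1.5 and √φ = 1.225. Then 1.96/1.225 = 1.600 and α = 11.0%.

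**Range.** Both r and k are assumptions. The simulation generated trials with no treatment effect, 165 per arm, 9% dropping out at a uniform time, and 6,000 trials per row. The test was unadjusted, on pooled events over person-time.

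| r per year | k | φ | α, formula | α, simulated | interval too narrow by |
|---|---|---|---|---|---|
| 0.3 | 0.2 | 1.12 | 6.4% | 6.3% | 6% |
| 0.3 | 0.5 | 1.30 | 8.6% | 8.4% | 12% |
| 0.3 | 1.0 | 1.60 | 12.1% | 11.9% | 21% |
| 0.5 | 0.2 | 1.20 | 7.4% | 7.1% | 9% |
| 0.5 | 0.5 | 1.50 | 11.0% | 10.5% | 18% |
| 0.5 | 1.0 | 2.00 | 16.6% | 16.2% | 29% |
| 1.0 | 0.2 | 1.40 | 9.8% | 8.9% | 15% |
| 1.0 | 0.5 | 2.00 | 16.6% | 16.4% | 29% |
| 1.0 | 1.0 | 3.00 | 25.8% | 26.6% | 42% |

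**Checks.** With k = 0 the simulated Poisson test holds its level (4.7% to 5.2%), so the excess comes from the heterogeneity and not from the simulation. On the same simulated data, dispersion-scaled and robust variances gave 4.5% to 5.9% in every scenario, including harsher ones (up to r = 1.5, k = 1.5) in which the plain Poisson test reached 40.1%.

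**The case against.** **The article may only be brief.** A journal article condenses a fuller protocol. Poisson regression can be fitted with a robust or scaled variance, and the analysis plan may say so. That is possible. But the article states the test rather than leaving it open, and followed as written it gives the model-based Poisson standard error. A rule that performs worse than a one-line alternative is a fair point to raise.

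**The model may be adjusted.** A reader might infer that the plan assumes the same rate for every patient. That is true only of an unadjusted model. If the five listed covariates enter, the assumption is equal rates given those covariates, and the sizes above, which come from an unadjusted test, would fall somewhat. This narrows the point. It does not remove it, because functional status and exacerbation history are not listed.

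**The inflation may be small.** A reader might also infer that the false-positive rate is certainly far above 5%. The article does not support that: it gives neither a rate nor a dispersion. Counted events are those needing an antibiotic or systemic steroid, in general-practice patients, so low rates cannot be excluded. At k = 0.2 and up to 1.0 per year the simulated size is only about 6% to 9%.

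**One tempting piece of evidence is weak.** The usual-care rule for patients with more than 2 exacerbations per year might be read as proof of unequal rates. It is a threshold on observed counts. With an identical Poisson rate of 1 per year, 1 − e⁻¹ × (1 + 1 + 0.5) = 8% of patients would still exceed it in a given year by chance. The point does not rely on it.

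**Conclusion.** The concern holds in a limited form. The stated test allows for no variation in rates beyond its covariates, and the article itself makes such variation likely. The p-value and interval for the exacerbation rate ratio are then too optimistic. Under the assumed 0.3 to 1.0 exacerbations per year and k of 0.2 to 1.0, the actual size is about 6% to 26%. The direction follows whenever unexplained heterogeneity exists; the amount cannot be derived from the article.

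The estimated rate ratio remains valid, and the primary SGRQ comparison and the sample size are untouched. Because this is a secondary outcome, the point should be fixed but is not critical.

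**What to change.** Amend the sentence on the exacerbation test to specify one of the following, with log person-time as offset:

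- Poisson regression with robust or dispersion-scaled standard errors, which was enough to restore the level in the check; or
- negative binomial regression.

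Fit the model to one record per patient, since two group totals alone carry no information on dispersion. Say whether the listed covariates enter it, and report the rate ratio with the resulting interval. Settle this before unblinding, so that the variance method is not chosen with the results in view. Adjusting for the previous year's exacerbation count, already collected at baseline, is an optional gain and is not needed to correct the test.

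The cost is one line of text, with no new data or patients. Intervals widen by the factor √φ: from 1.06 (φ = 1.12) to 1.73 (φ = 3.0) over the range shown, and hardly at all if the counts prove not to be overdispersed.

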### Duration

Patients will be followed up for 2 years and during that period there will be 7 visits, including a baseline and a final visit (Figure 1).

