### Measurements

#### Baseline visit and last visit

At each visit, the disease should be stable; in case of an exacerbation visits are postponed, there should be at least 6 six weeks between the end of the exacerbation and the visit. The following parameters are gathered at baseline and last visit:

•Patient demographics: age, gender, marital status, educational level, employment status.

•COPD specific information: smoking status, pack years, duration of COPD.

•Previous participation in a formal smoking cessation program, pulmonary rehabilitation or reactivation program.

•Co-morbidities, using the Charlson comorbidity index [29].

•Medication use and exacerbations in the last year. Exacerbations are defined as an increase in or new onset of more than one respiratory symptom (cough, sputum, sputum purulence, wheezing, dyspnea) with a duration of two or more days requiring treatment with an antibiotic and/or systemic steroid [30].

•Spirometry, pre- and postbronchodilator FEV_1_ in liters, FEV_1_ % predicted, FVC %predicted, and inspiratory capacity. The bronchodilator will be administered as salbutamol 4 times 100 microgram per metered dose inhaler with chamber device.

•Body Mass Index

•Functional exercise capacity as measured by the 6 minute walking test [31]. The patients are asked to walk up and down a level 30 meter walkway for 6 minutes. Breaks are allowed if necessary and recorded. Total distance walked is recorded as well as heart rate, blood pressure, Borg dyspnea score and oxygen saturation immediately before and after the test.

•Patient reported outcomes:

•The SGRQ is a 50-question, 76-item, health status scale for COPD patients. The SGRQ has 3 subscales: symptoms, activities and impact. The score ranges from 0 (best) to 100 (worst). The minimal clinically important difference is 4 points [32,33].

•The Clinical COPD Questionnaire is a 10-item health status scale measuring three domains: symptoms, functional status and mental state of COPD patients. Scores range from 0 (best) to 6 (worst). The minimal clinically important difference is 0.4 [34,35]. The CCQ has also been validated on the individual patient level [15].

•The modified Medical Research Council (mMRC) dyspnea scale [36]. This measures dyspnea on a scale of 0 (not breathless except when performing strenuous exercise) till 4 (too breathless to leave the house or breathless when dressing).

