### During each follow-up visit

The following is collected during each follow-up visit: spirometry, pulmonary medication use, generic questionnaire about treatment offered and received, unscheduled visits to the GP or hospital because of pulmonary problems and patient reported outcomes: CCQ, SGRQ, mMRC, EuroQOL-5D and HADS.

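### The primary analysis reduces seven scheduled SGRQ measurements to one change score, so the method named does not by itself secure the intention-to-treat principle

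*Protocol article*

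**What the plan says.** All references are to the protocol article.

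- **Schedule.** Under Duration, "during that period there will be 7 visits, including a baseline and a final visit". SGRQ is on the list introduced by "The following parameters are gathered at baseline and last visit", and the section on follow-up visits lists "patient reported outcomes: CCQ, SGRQ, mMRC, EuroQOL-5D and HADS". SGRQ is therefore planned at every visit.
- **Primary comparison.** The primary outcome is change in SGRQ over time. Under Statistical analysis, "The SGRQ change in scores over the treatment period of the control group will be compared to that of the experimental group".
- **Method.** If the scores are normally distributed, "the difference will be univariately tested with a student T-test and multivariately with a linear regression model"; otherwise the same tests follow a Box-Cox transformation. The regression adjusts for education, age, gender, current smoking and FEV1. Baseline SGRQ is not on that list, and no repeated-measures model is named.
- **Analysis principle.** "The primary analyses will be based on the intention-to-treat principle", with a per-protocol analysis as secondary.
- **Sample size.** 150 per group are needed, and "Taking dropouts into consideration, a sample size of 165 patients / group = 330 patients in total is aimed for".

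**The concern.** A t-test or regression on change over the treatment period takes one number per patient. A patient who leaves before the last visit has no such number unless one is imputed, even when up to five intermediate SGRQ scores were collected. The article names an all-randomised principle together with a method that cannot carry it out unaided.

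It matters because missing final scores are plausibly related to the outcome. The Discussion says that functional status, as measured in health status questionnaires, predicts exacerbations, admissions and mortality. Mortality is a secondary outcome, and a patient who dies has no final SGRQ. Visits are postponed after an exacerbation, which could make a final visit harder to obtain in unstable patients. If those without a final score fared worse, and their number or their deficit differs by arm, a comparison of those who remain is biased. The intermediate scores are the data that could reduce this bias, and the named models leave them out.

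**Working it through.** **1. Scores available.** Seven visits less baseline and final leaves 7 - 2 = 5 intermediate visits. Six intervals in 24 months is one every 4 months, which agrees with the four-monthly advice described in the Abstract.

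**2. What the named model can use.** The analysed quantity is D = SGRQ(final) - SGRQ(baseline). That reading follows from the wording on change over the treatment period and from the Discussion, which gives the objective as the effect after two years. D does not exist without a final score, and intermediate scores do not enter it.

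**3. The plan's own figures.** Inputs under Sample size calculation: "Based on 80% power to detect the minimal clinically important difference (4 points on the SGRQ) between the two groups", SD 12, alpha 0.05 (two-sided assumed, as sidedness is not given).

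- n per group = 2 x (1.960 + 0.842)^2 x 12^2 / 4^2 = 141.3, so 142 (143 by exact t-test). The stated 150 is about 5% larger, which is conservative and does not bear on this point.
- 150 x 1.10 = 165. The loss that leaves 150 per group is 15/165 = 9.1%, or 30 of 330 patients.

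Power if only patients with a final score are analysed, starting from 165 per group, is approximately Phi(4 / (12 x sqrt(2/n)) - 1.960):

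| Loss | n per group | Power |
|---|---|---|
| 9.1% | 150 | 82% (2.887 - 1.960 = 0.927) |
| 15% | about 140 | 80% |
| 20% | 132 | 77% |
| 30% | about 116 | 72% |

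At the top of the article's SD range (17), power is much lower, but the fall from 165 to 150 per group costs only about 4 percentage points (57% to 53%). Lost power is not the reason to change the analysis.

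**4. Size of the bias, by formula.** Let p be the proportion in an arm without a final score, and g the amount by which their two-year change would have been worse than that of patients with one. The mean of those with a final score understates the arm mean by p x g. With lower SGRQ better, the error in (intervention - control) is p_control x g_control - p_intervention x g_intervention. If g is the same in both arms, this is (difference in p) x g:

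- Assumed differences of 5-10 percentage points and g of 4-12 SGRQ points give 0.05 x 4 = 0.2 up to 0.10 x 12 = 1.2 points.
- If p and g are equal in both arms, the error is zero.
- More loss in control pulls an effect of -4 towards zero. More loss in the intervention arm exaggerates it.

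None of these values of p or g is in the article.

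**5. Size of the bias, by simulation.** Both simulations have 7 visits, 165 per arm and a true 24-month difference of -4.0. Dropout depends on the patient's observed SGRQ worsening. The settings are assumptions. The first uses SD 14 and a baseline-to-24-month correlation of 0.61, with 1,500 repetitions. The second uses equal correlation 0.6 and a change SD of 12, with 600 repetitions.

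| Dropout rule | Dropout | Final score only | Likelihood, all visits |
|---|---|---|---|
| Same in both arms (first) | 8-19% | about -3.8 to -3.95 | -3.9 to -4.0 |
| Same in both arms (second) | 26% control, 22% intervention | -3.7 | -4.0 |
| Worsening-driven in control only (second) | 26% control, 15% intervention | -2.1 | -3.9 |

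With the same rule in both arms, the error is 0.05 to 0.2 points at 8-19% dropout and 0.3 points at 22-26%. The last row shows that it can become large, but only under a one-sided mechanism and with control-arm loss of 26/9.1 = 2.9 times the planned loss.

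**The case against.** The strongest reply is that the article never says patients without a final visit are dropped. That is correct. A reader might infer that the primary analysis is a completers analysis that contradicts the intention-to-treat statement. The text does not support this: multiple imputation from the intermediate visits, or use of the last available score, would fit the same t-test and regression. Rules for missing data are commonly left to a full protocol or analysis plan, neither of which is shown, so the lack of such a rule is no fault here.

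A reader might also take the step from 150 to 165 per group as proof of exclusion. It is not. Dropout costs information under imputation and mixed models too, so sample sizes are inflated under any of these methods.

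Nor can a bias of 1.2 points, or 30% of the 4-point target, be presented as expected. It needs a 10-point difference in dropout together with a 12-point deficit. At an average loss of 9.1%, that means about 4% against 14% by arm. The article gives no reason to expect this. It describes patients and doctors as blinded and says the experimental treatment does not differ markedly from usual care.

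Finally, a t-test with adjusted regression on change is a valid choice, and a mixed model also leaves out patients with no post-baseline score. Both statements stand. What they do not answer is that the article itself fixes the primary model, and that this model has no place for five scores per patient that will be collected anyway and that can reduce bias when dropout depends on observed worsening.

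**Conclusion.** The point holds as a cheap improvement to the primary method, not as an internal contradiction. With SGRQ planned at seven visits, the named t-test and regression use one change score, ignore the intermediate scores and, without imputation, admit only patients with a final SGRQ. The method named therefore does not secure the intention-to-treat principle.

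The expected size is modest: about 0.05-0.3 points against a target of 4 when the same dropout rule applies in both arms. A material bias, such as -2.1 in place of -4.0, requires outcome-related dropout that differs by arm, which is an assumption. The advantage of using all visits holds when dropout depends on observed scores. It is not guaranteed when dropout depends on unobserved ones.

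**What to change.** - Make the primary analysis a mixed model for repeated measures on SGRQ total at all post-baseline visits, with treatment x visit, baseline SGRQ x visit, the covariates already listed, and an unstructured covariance. The 24-month treatment contrast is the primary estimate.
- Include every randomised patient with at least one post-baseline SGRQ in the allocated arm. Report by arm the number left out for having none.
- Add a delta-adjusted sensitivity analysis for dropouts and deaths that worsens their imputed scores by a range of amounts, set separately by arm.
- Keep the change-score t-test and linear regression as sensitivity analyses, and state how patients without a final score enter them.

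**Cost.** Analysis work only, since no visit or measurement is added. The model relies on missing at random, which the delta-adjusted analysis probes, and it still omits patients with no post-baseline score.

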## Discussion

The objective of the MARCH study is to study whether a treatment algorithm that is based on health status as measured by CCQ improves health status as measured by SGRQ after two years of use compared to care based on FEV_1_ levels as per regular (GOLD) guidelines.

This study is based on the assumption that treatment based on problems that matter to patients (as reflected in a health status measurement) will have more positive effect on their life than treatment that is based on a single measurement that has little relation with their problems (FEV_1_).

The selection of an appropriate primary outcome measure for the current study was an important issue during the design process. The traditional primary outcome measure in COPD research is lung function, usually represented by the FEV_1_. The US Food and Drug Administration (FDA) and the European Medicines Association (EMA) still routinely require this in pharmaceutical trials. However, FEV_1_ has been found to have a very poor correlation with markers of COPD that seem to matter most to patients, such as exercise tolerance, symptoms and also health status [46,47]. Therefore, currently most researchers regard changes in patient centered outcomes such as health status, symptoms, exacerbations and functional status more important than changes in lung function [47]. Patient centered outcomes better reflect the complexity and the impact of the disease, and several aspects of health status predict clinically meaningful outcomes in COPD [48,49]. For instance, functional status as measured in health status questionnaires has been shown to predict exacerbations [50,51], hospital admissions [50-54] and mortality [55,56]. In most large scale COPD studies, health status is measured and demonstrated to improve after successful interventions, but it is seldom used as primary outcome. The situation is different in pulmonary rehabilitation studies where health status has been used as one of the primary endpoints [57].

Using health status as primary outcome measure in a study where the treatment in one arm is organized according to health status carries the risk of direct influence on the outcome. In order to reduce this potential methodological problem, a different health status questionnaire (SGRQ) is used in our study instead of the questionnaire that is used to guide the treatment (CCQ).

In the current study we decided to randomize on the patient level and not on the GP cluster level. This decision was made after careful evaluation of advantages and disadvantages of randomization on the individual and the cluster level. In this evaluation the following factors played a pivotal role. A large disadvantage of cluster randomization is the risk of selective inclusion, i.e. the physician is more likely to discover to which treatment group all his or her patients are allocated and this might, unconsciously, play a role in selecting patients for participation in the study. A second large disadvantage is the need for a much larger study population to maintain sufficient power. An additional power calculation assuming 10 COPD patients per practice, and a correlation of SGRQ within primary care practices scores of 0.14 (based on previous unpublished studies in our group), the total number of patients needed to achieve a power of 0.8 is 462. This constitutes an increase in patient number of 40%.

A disadvantage of randomizing at the individual level is the risk of contamination, loss of allocation concealment. This risk is present on both the patient level and on the physician level. On the patient level this is caused by the fact that several patients from one GP practice participate in this study and often patients in one practice know each other. Therefore patients in the control group might know patients that have been randomized into the intervention group and via that route receive information from the intervention group which they then might decide to use for themselves. However, we do not consider this to be a large risk in our study because the experimental treatment does not differ markedly from the usual care treatment, the same treatment elements are used albeit differently organized. In other words none of the patients will receive completely new and unexpected advices and therefore we expect them to conform to the recommendations given by their physicians.

The second level on which contamination might pose a risk for the study is the physician level, physicians might learn from the intervention and adjust their way of working. We try to circumvent this risk by supplying the physician with clear and individually tailored written practical advices. Physician and patients are routinely asked to report which treatment was given to each of the participants in the study giving us an accurate picture of whether or not contamination was present and if so the size of the problem.

Health care providers are not used to interpreting health status data. They need education and support to learn how to interpret the scores of health status instruments if they are to be successfully integrated into routine practice. Greenhalgh’s review of health status studies concluded that information should be fed back throughout the decision making process to all clinicians involved in the patient’s care and in a format they can make sense of and integrate in clinical decision making [23]. Health status scores should therefore be presented in a coherent clinically relevant format, with clear guidelines for interpretation and preferably with to-the-point recommendations. Based on Greenhalgh’s suggestions we incorporated in our study a clear treatment advice for the participating clinicians in order to avoid difficulties around the interpretations of health status scores.

Much effort was put in designing the treatment algorithms, because this is a pivotal part of the study design. During the design process choices without supporting evidence had to be made, this is because treatment based on health status is a novel concept and all previous studies were based on impairment of lung function as treatment criterion. By discussing the algorithm in different settings and with partners from various backgrounds we tried to reduce possible bias.

Vital for successful completion of the study is compliance of the care provider with the treatment advices. In the current Dutch GP practice the care for patients with chronic diseases is often transferred from the GP to the practice nurse. This applies also to implementing treatment advices. Practice nurses can achieve similar outcomes as doctors in chronic disease management [58]. Additionally, it has been demonstrated that practices in which the organization is optimal, guidelines are better adhered to [59]. Although this adds an extra layer in the process from measurement (lung function or health status) to effectuating the treatment, we are confident that in well organized practices with practice nurses, our advices will lead to similar results as with practices that do not work with practice nurses.

